**Trial registration number:**

NCT03441906.

Strengths and limitations of this studyThe international design allows for comparison of healthcare systems and its influence on total interval length.Multicentre, prospective design allows reliable comparison of sarcoma subgroups to make clinically relevant recommendations to improve total interval.Inclusion of patients at diagnosis minimises recall bias for total interval length.Patients were actively involved in the design of this study and mentioned earlier diagnosis and patient-reported outcomes as research priorities.

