Possible risk factors for a prolonged total interval could be patient, tumour or healthcare system characteristics. In order to study the latter, it is informative to compare patients from different countries. In both the Netherlands and UK, general practitioners (GPs) have an important role as healthcare gatekeepers. In general, people consult their GP who then decides whether referral is warranted and determines the acuteness and location of the referral. In the UK, privately insured patients can also self-refer to a hospital without seeing a GP. Furthermore, within the UK, a considerable amount of patients with cancer is diagnosed at an emergency department, associated with worse outcomes.^11^ Sarcoma care is formally centralised within the UK, whereas the Netherlands has bone sarcoma centres, and referral to dedicated STS centres is encouraged, but not commissioned. Furthermore, cultural differences may play a role in patient behaviour. Also, longer travel time to a sarcoma centre in the UK compared with the Netherlands may also affect total interval length.

Up to now, only few studies regarding total interval length and clinical outcomes in sarcoma have been published, most were retrospective and included mainly children. Some studies found that a longer total interval worsened OS, while others did not find inferior clinical outcomes.^10^ Researchers have argued that this lack of an association, often referred to as the ‘waiting-time paradox’, may be because the studies have not been able to adequately adjust for the aggressiveness of the cancer tumours. The most significant effect of a long interval for sarcomas seems to be the increasing size of the lesion,^12^ with consequent decreased chance of uncomplicated resection with clear surgical margins, a greater risk of amputation and increased risk of developing metastases.^13^ This may also affect patient-reported outcomes such as HRQoL of patients with sarcoma.

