### Total interval

A 42-item list was self-designed to assess the total interval. Examples of questions are as follows: ‘With which symptom(s), caused by the sarcoma, did you first go to a doctor?’, ‘To which doctor did you first talk about your symptoms?’ and ‘How often did you talk to the following doctors about your symptoms belonging to sarcoma, before you heard you had a sarcoma?’ At follow-up, a few questions are repeated to complete data collection. We will sample survey the reported dates by cross-checking them with the patient’s record. If more than 5% of the cross-checked dates deviates more than 1 month from the registered dates in the medical record, we will cross-check all dates and use the clinical reported dates for statistical analysis.

Health literacy is being assessed by a Dutch adaptation of Chew’s Set of Brief Screening Questions (SBSQ) in a single-item question.^23–25^

Social support is being assessed by one single item: ‘Was the amount of support you received from others sufficient?’ extracted from the Quality of Life-Cancer Survivors questionnaire.^26 27^

Self-efficacy is measured with the General Self-Efficacy scale (GSE).^28^ This 10-item scale assesses a general sense of perceived self-efficacy with the aim to predict coping with daily hassles as well as adaptation after experiencing a stressful life event. Self-efficacy is the belief that one can perform a novel or difficult task, or cope with adversity. Perceived self-efficacy facilitates goal-setting, effort investment, persistence in face of barriers and recovery from setbacks. Responses are made on a 4-point scale. A higher final composite score correlates with higher perceived self-efficacy.

Coping is assessed in the 3-month questionnaire with the help of the brief Coping Orientation to Problems Experienced (COPE).^29^ Coping is about emotional and mental reactions, which enable people to activate sources of help needed to cope with stress and problems. This 28-item scale measures 14 positive and negative styles of coping on a 5-point Likert-scale.

Resilience is measured in the 6-month questionnaire using the Brief Resilience Scale (BRS).^30^ Resilience is a skill that helps people recover from a life event. People with high (perceived) resilience can move on faster after a setback. The BRS is a 6-item scale with a 5-point Likert scale.

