### Statistical analysis

Descriptive statistics (means, SD, median, range, frequencies) will be used to quantify diagnostic intervals and describe the study population.

HRQoL at baseline will be calculated according to the EORTC scoring manual.^43^ Missing items will be imputed according to these guidelines, after which an available case analysis will be performed.

The relationship between total interval length and HRQoL at baseline will be investigated by plotting HRQoL against total interval length as a continuous variable. Linear regression will be used to assess their association. The time point providing a significant difference in HRQoL will be used as a cut-off point for further analysis. If this does not provide a clear cut-off point, logistic regression will be used to assess an association between baseline HRQoL and total interval grouped into suitable categories, such as quartiles. The last quartile will then be used to define the population with a long interval.

Apart from statistical significance, we will look at clinically relevant differences in HRQoL scores as determined by Cocks *et al.*^42^ A small effect size will then be considered as an appropriate value for a cut-off point.

A series of univariate logistic regression analyses will be conducted to assess the relationship between total interval length (grouped by the cut-off point as defined by the previous analysis) and independent variables, such as patient, tumour and healthcare system risk factors. All factors with p<0.1 will then be used in multiple logistic regression analysis (forced entry method) to investigate whether these factors are independently associated with total interval length.

Apart from total interval length, the association of other patient and tumour characteristics (such as self-efficacy, social support, financial difficulties, histology), and HRQoL at baseline will be investigated using univariate logistic regression analysis. Using the forced entry method, multiple logistic regression analysis will then be performed with all factors with p<0.1 to assess what factors are independently associated with baseline HRQoL.

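### No stated analysis gives a case-mix-adjusted total country difference in interval length: the one adjusted model admits country only by p-value and may condition on pathway factors

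*Protocol article*

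**What the plan says.** Three places in the protocol article make the country comparison a purpose of the design.

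- The strengths and limitations list says the "international design allows for comparison of healthcare systems and its influence on total interval length".
- The Introduction names patient, tumour and healthcare-system characteristics as possible causes of a long interval, and says of the last group: "In order to study the latter, it is informative to compare patients from different countries".
- The Sample size calculation section sets 265 patients in each country so that the countries can be compared.

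The Introduction also describes how the two systems differ. GPs act as gatekeepers in both countries, but "In the UK, privately insured patients can also self-refer to a hospital without seeing a GP", and "within the UK, a considerable amount of patients with cancer is diagnosed at an emergency department". Sarcoma care is formally centralised in the UK and less so in the Netherlands. Finally, "longer travel time to a sarcoma centre in the UK compared with the Netherlands may also affect total interval length". Cultural differences are mentioned as well.

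The Total interval section shows that some pathway information is collected. One item is "To which doctor did you first talk about your symptoms"; another asks how often each type of doctor was consulted before the diagnosis was known.

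For interval length, the Statistical analysis section first fits univariate logistic regressions on "independent variables, such as patient, tumour and healthcare system risk factors". Then: "All factors with p<0.1 will then be used in multiple logistic regression analysis (forced entry method"). The aim of this second model is to see which factors are independently associated with interval length.

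**The concern.** First doctor seen and number of consultations are partly produced by the healthcare system, and they in turn affect how long diagnosis takes. They lie on the path from country to interval. A model holding both country and these measures estimates the part of the country difference that does not run through them. That is a legitimate quantity, but it is not the difference between the two systems.

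The only other country estimate described is the univariate one. It carries any difference between the national samples in age, histology or the mix of bone and soft tissue sarcoma. It could show a country difference that is really case mix, or hide a true one.

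At stake is the comparison that the strengths list and the two-country recruitment target are there to support. A weak country coefficient in the adjusted model could be read as similar performance of the two systems when it only means that the measured pathway explains the gap.

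**Working it through.** The article gives no figure on this point to reproduce. The 265 per country is used below only as a sample size; nothing depends on how it was derived.

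**Step 1. Which stated analyses could supply the adjusted country difference in interval length?**

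| Analysis | Adjusted for case mix? | Free of pathway factors? | Country certain to be estimated? |
|---|---|---|---|
| Univariate logistic regression | No | Yes | Only if country is among the candidates; it is not named |
| Multiple logistic regression after the p<0.1 screen | Only for case-mix factors that pass | Not assured; none are excluded | No, country must pass p<0.1 |
| Subgroup analyses by geographical area (Endpoints section) | Not stated | Not stated | No; conditional on subgroup size, and an analysis within one country contains no country contrast |
| Models correcting for healthcare system (later in Statistical analysis) | Different question | Different question | Interval is the exposure there, not the outcome |

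No row gives the case-mix-adjusted total country difference.

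**Step 2. How far can conditioning on pathway factors move the country coefficient?**

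All effect sizes in this step are assumptions.

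Inputs: 530 patients, half per country; three pathway factors that differ by country, namely a continuous one with a mean difference of 0.7 SD and two binary ones (10% v 25% and 10% v 20%).

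Model: logit P(long) = −1.6 + d × country + s × (0.4 × continuous + 0.8 × binary₁ + 0.8 × binary₂).

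The p<0.1 screen and simultaneous entry are then applied as the article describes, in 600 replicates. The adjusted odds ratio (OR) is the median over replicates in which country entered. The significant shares are of all replicates.

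| Scenario | d, s | True direct OR = exp(d) | Unadjusted OR | Adjusted OR | Significant, unadjusted → adjusted | Country passes screen |
|---|---|---|---|---|---|---|
| Fully mediated | 0, 1 | 1.00 | 1.62 | 1.07 | 65% → 3% | 75% |
| Partly direct | 0.3, 0.6 | 1.35 | 1.78 | 1.40 | 81% → 27% | 88% |
| Wholly direct | 0.55, 0 | 1.73 | 1.71 | 1.73 | 72% → 66% | 81% |

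The adjusted model recovers roughly the direct effect. In the first two rows it lies slightly above it, as expected when only replicates that passed the screen are counted. In the wholly direct row nothing shrinks, so the attenuation in the other rows comes from conditioning on the pathway. In 12% to 25% of replicates (100 − 88 and 100 − 75) country fails the screen and there is no adjusted country estimate.

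**Step 3. A second simulation as a check.**

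Assumptions: 265 per country; long interval defined as the pooled top quartile; a total country shift of 0.45 SD on log interval; one pathway factor differing by 0.8 SD between countries.

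- Country plus case mix: OR about 2.0 to 2.1, significant in 91% to 97% of runs.
- Pathway factor added, carrying 50%, 75% or 100% of the effect: OR 1.48, 1.21 or 1.00, significant in 42%, 13% or 5%.
- Pathway factor added, carrying none of it: no attenuation.

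**Step 4. Can the univariate estimate stand in?**

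Assume no country effect, bone sarcoma shares of 15% v 40%, and an interval 0.6 SD longer in bone sarcoma. The univariate country OR is then 1.30 and is significant in 26% of runs, against a nominal 5%. These shares are also assumed; the article gives no case mix by country.

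**The case against.** A reader might infer that the plan forces country into a model with travel time, referral route and first doctor, so that the healthcare-system effect is bound to be adjusted away and a real difference reported as absent. The article does not support that.

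- Country is not named as a covariate. Forced entry means that all factors passing the screen go in together, not that country is kept.
- Travel time and emergency presentation appear in the Introduction as background and are not listed among the data collected. First doctor and consultation counts are the pathway items shown, and the article does not say outright that they are candidates.
- The coefficient falls to about 1 only under full mediation. With no mediation it does not move.
- Mutual adjustment is coherent for finding independently associated factors, which is the model's stated aim. If first doctor carries the country effect, its own coefficient is a healthcare-system result, so the difference is reattributed rather than lost.
- None of the simulated effect sizes comes from the article, and the mechanisms in the Introduction could act in opposite directions.

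It can also be said that a journal article condenses the full plan, and that a country model may exist elsewhere. That would answer a complaint about missing detail. Here, however, the article states a procedure, a p-value screen followed by one all-in model, and that procedure does not deliver a comparison the same article names as a strength. The point stands in this limited form.

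**Conclusion.** The point holds as a gap between a stated purpose and the stated analysis. The article presents the two-country design as a way to compare healthcare systems, yet neither the univariate regression nor the screened all-in model gives the case-mix-adjusted total country difference in interval length. If country enters with pathway measures, its coefficient is residual.

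The size cannot be fixed from the article. Under the assumptions shown, attenuation runs from none (wholly direct effect) to an odds ratio near 1 (full mediation). The conclusion assumes that pathway items such as first doctor are candidates under the healthcare-system heading and that some pass the screen. It does not show that a country effect exists or that it would be missed. The analyses of HRQoL, PFS and OS are untouched, so this should be corrected for the healthcare-system aim and does not threaten the primary endpoint.

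**What to change.** In the Statistical analysis section, add two fixed models for interval length.

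1. **Country model.** Regress the interval outcome on country plus prespecified patient and tumour factors (for example age, sex, bone v soft tissue, histology group and anatomical site). Keep all of them, country included, whatever their p-values, and include no pathway factors. Report the country coefficient as the adjusted country difference. Say that it combines healthcare system with other national differences, such as the cultural ones in the Introduction, and is not a pure healthcare-system effect.
2. **Pathway model.** Add whichever pathway factors are collected, such as first doctor seen and number of consultations. Report their coefficients as healthcare-system findings. State that the country coefficient in this model is residual and is not the country comparison.

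The screened model can remain as the exploratory search for associated factors. The cost is plan wording and one extra regression on data already planned, with two models to report and explain instead of one.

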### Health-related quality of life

HRQoL is being assessed with the EORTC QLQ-C30, V.3.0, which is validated and available in English and Dutch.^31^ This 30-item HRQoL questionnaire consists of five functional scales (physical, role, cognitive, emotional and social), a global quality of life scale, three symptom scales (fatigue, pain, nausea and vomiting) and a number of single items assessing common symptoms (dyspnoea, loss of appetite, sleep disturbance, constipation and diarrhoea) and perceived financial impact of the disease. After linear transformation, all scales and single-item measures have scores ranging from 0 to 100. A higher score on the functional scales and global QoL means better functioning and HRQoL, whereas a higher score on the symptom scales means more complaints.

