### Endpoints

The primary endpoint is HRQoL of patients with sarcoma at diagnosis (baseline) as measured with the EORTC QLQ-C30 (global health status). Secondary endpoints are: QALY, psychological distress, stage and tumour size at diagnosis, PFS and OS.

If subgroups are large enough, we will conduct these analyses for different clinically relevant subgroups, such as different histological subtypes, geographical areas, and so on.

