### Sample size calculation

We expect a minimum response rate at baseline of 65%, based on rates in other PROFILES studies.^40^ During follow-up, after completion of the first questionnaire, we expect a response rate of 80%. The definition of a long total interval will follow from our statistical analysis (see below), however, if the analysis does not provide a clear cut-off point, we will use the last quartile to define the population with a long total interval.

Using the EORTC QLQ-C30, differences of at least 10 points have been considered as clinically meaningful.^41^ Based on results from our ongoing PROFILES studies, an SD of about 20 points for each scale can be expected. Using an alpha of 0.05, a power of 0.90 and a long diagnostic interval of 25% in the total group of patients with sarcoma, with the expected drop-out, would require 265 patients.^42^ In order to make country-to-country comparisons, we aim to include 265 Dutch and 265 English patients in a time frame of 18 months with a total follow-up of 24 months.

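### Logistic regression is named for factors associated with baseline HRQoL, a 0-100 score that the plan elsewhere analyses by linear regression and nowhere divides into categories

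*Protocol article*

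**What the plan says.** In the Protocol article, the Endpoints section makes baseline global health status on the EORTC QLQ-C30 the primary endpoint. Under Health-related quality of life, "all scales and single-item measures have scores ranging from 0 to 100". The Sample size calculation treats the score as quantitative: 10 points is the clinically meaningful difference, and "an SD of about 20 points for each scale can be expected".

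The Statistical analysis section then gives three treatments of baseline HRQoL:

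- Against total interval as a continuous variable: "Linear regression will be used to assess their association".
- If no clear interval cut-off emerges: "logistic regression will be used to assess an association between baseline HRQoL and total interval grouped into suitable categories, such as quartiles".
- Against characteristics other than the interval, such as self-efficacy, social support and histology: "HRQoL at baseline will be investigated using univariate logistic regression analysis", and then "multiple logistic regression analysis will then be performed with all factors with p<0.1 to assess what factors are independently associated with baseline HRQoL".

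**The concern.** Logistic regression models a categorical outcome. The third treatment applies it to a 0-100 score without naming a category, although the same section handles that score linearly against total interval. Three things are at stake.

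- Read as binary logistic regression, the model can be run only after the primary endpoint has been cut in two, which discards information. The p<0.1 screen for the multiple model would then rest on the weaker test.
- The position of the cut is not fixed in this document.
- Total interval would be reported in points and every other factor as an odds ratio for the same endpoint. The two could not be compared with each other, and the odds ratios could not be judged against the 10-point difference that the plan uses for clinical relevance.

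**Working it through.** **1. Which variable is the outcome.** The multiple model is run "to assess what factors are independently associated with baseline HRQoL", so HRQoL is the dependent variable and the factors are predictors. An earlier paragraph uses the same sequence (univariable logistic regression, p<0.1, forced entry) for total interval grouped at a cut-off. That outcome has two levels, so the method fits there. The HRQoL paragraph repeats the sequence for an outcome it does not fit.

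**2. Whether HRQoL is divided anywhere.** The Sample size calculation and Statistical analysis sections mention a cut-off derived from the HRQoL plot and, failing that, the last quartile. Both define a long total interval, on the time axis. No threshold is given on the 0-100 scale.

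**3. The plan's own figure.** The factor analysis has no power target. The only sample-size figure is 265 per country, including drop-out, for long versus short interval. From the stated inputs (10 points, SD 20, two-sided 0.05, power 0.90, 25% long):

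- N = (1.960 + 1.282)² × 20² / (10² × 0.25 × 0.75) = 224.2, or 228 when rounded to whole groups of 57 and 171.
- At the stated 65% baseline response this becomes 228 / 0.65 = 351.

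The 265 is therefore not reproduced. That is a separate matter, and nothing below depends on it.

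**4. Information lost by a binary split.** Assume a normal score. For an event share p, efficiency relative to a comparison of means is φ(z_p)² / [p(1 − p)].

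- Median split: 0.3989² / 0.25 = 0.637, a loss of 36%.
- Quartile split: 0.3178² / 0.1875 = 0.539, a loss of 46%.
- Ordinal (proportional-odds) model, no split: 3/π = 0.955, a loss of about 5%.

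**5. Check at a full 10-point effect.** Take an illustrative factor present in 25% of patients, with a 10-point lower mean and SD 20. For 90% power:

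| Analysis | Proportion below the cut (factor present / absent) | Evaluable N | Loss |
|---|---|---|---|
| Score kept | – | 228 | – |
| Median split | 0.647 / 0.451 | 356 | 1 − 228/356 = 36% |
| 25% event share | 0.377 / 0.208 | 392 | 1 − 228/392 = 42% |

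The quartile loss is somewhat smaller here than in step 4 because that formula is a small-effect approximation.

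**6. Dependence on shape.** At the median, the loss is 18% for a logistic-shaped score, 4% for a t distribution with 5 degrees of freedom and 67% for a uniform score. A simulation with 228 patients used a rounded score bounded at 0 and 100, with 13 levels assumed. Power was 0.89 to 0.91 for the t-test, 0.88 to 0.89 for the Wilcoxon test (the analogue of the ordinal model), 0.74 to 0.76 for the median split and 0.72 to 0.74 for the quartile split. Rounding and bounding a near-normal score therefore do not remove the loss.

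**7. Scale of the result.** The same 10-point difference in step 5 gives an odds ratio of (0.647/0.353) / (0.451/0.549) = 2.23 at the median and (0.377/0.623) / (0.208/0.792) = 2.30 at the quartile. Neither can be read back as 10 points without knowing the cut and the SD.

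**The case against.** The strongest reply is that the article condenses a fuller protocol and analysis plan, and that an HRQoL threshold may stand there. This holds to the extent that the missing threshold is not a finding by itself. It does not remove the conflict, because the article actively names a model at odds with its own linear analysis and mean-based sample size for the same score.

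Four stronger readings may tempt a reader, and the documents do not support them.

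- *The analysis must lose at least a third of the information.* The text says logistic regression and never says binary. An ordinal model would lose about 5%, and the 36% minimum for a binary split assumes a normal score, which the article does not state.
- *The fallback on interval quartiles contains the same error.* That sentence does not say which variable is the outcome. With interval category as the outcome, HRQoL need not be cut, although four quartile groups would call for an ordinal or multinomial model or for collapsing to two.
- *The planned 90% power falls to about 73%.* The 90% belongs to the long-versus-short interval contrast, which is first analysed linearly. The factor paragraph expressly sets total interval aside.
- *265 patients act like 169* (265 × 0.637). The 265 is a per-country target that already allows for drop-out, so it is not the number analysed.

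**Conclusion.** The point holds in limited form. For factors associated with baseline HRQoL, the article prescribes a model that does not match a 0-100 outcome and contradicts its own treatment of that outcome. Under the ordinary binary reading and a roughly normal score, the cost is about 36% of the information at a median split and 46% at a quartile split, plus results on a scale that cannot be set beside the 10-point difference or the linear interval results. The sample sizes in the working are benchmarks for an assumed factor present in a quarter of patients, not the power of any named factor.

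The clear error is confined to the factor analysis. The main interval-HRQoL association is linear and the longitudinal HRQoL analysis uses mixed models, so neither is touched. The fallback sentence is ambiguous rather than wrong.

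**What to change.** In the paragraph on factors other than total interval, replace univariate and multiple logistic regression with univariable and multivariable linear regression on the 0-100 global health score. Report mean differences with 95% confidence intervals, and use robust standard errors if ceiling effects appear. A named ordinal model is an acceptable alternative. If a binary HRQoL outcome is really wanted, state and justify its threshold in advance.

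In the fallback sentence, state which variable is the outcome. If it is HRQoL, regress the score linearly on interval quartile. If it is interval category, name the binary, ordinal or multinomial model. Logistic regression for the two-level long-interval outcome can stay.

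The change needs no new data or software. The small downside is that ceiling effects can distort mean differences, and robust standard errors do not correct that. The ordinal model is the alternative if the ceiling proves marked.
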